### Recruitment

Contact persons of different MS clinics in German hospitals were contacted by the project leader (CH) and informed about the study. All outpatient clinics which were willing to participate have been included in the study. Recruitment strategies will be individualised to ensure that centres’ specific requirements are addressed (please see screening visit). The feasibility of recruitment is currently being tested in the pilot study.

### Allocation

Clusters will be stratified by type of hospital (university hospital or community based hospitals). Allocations will be computer generated and will be performed by a statistician not involved in the conduct of the trial. Prior to randomisation of the centres, contextual factors of the participating centres will be assessed in a baseline survey.

Centres will be aware of their allocation status. To minimise selection bias, patients will not receive explicit information about their allocation group, but will only be informed that they will be assigned to one of two methods of information provision about MS immunotherapy (information provision only or information provision plus information by a nurse).

### Blinding

Blinding of patients in patient information trials is difficult as the intervention can be easily detected. Therefore, due to the nature of the intervention it is not possible that clusters and patients are blinded. Nevertheless, contamination is avoided by the cluster design and patients will only be informed that two different ways of decision support regarding immunotherapy, information provision only or information provision plus information by a nurse, will be assessed. Assessment of the endpoints will be evaluator blinded as persons concerned with outcome assessment (by telephone interviews) will not be informed about patient and centre allocation.

### Data collection methods

Data will be collected at seven time points using web-based questionnaires (see Table 1). Use of the web platform will be explained via information sheets and through personal information within the study centres. Additionally, some data will be collected by telephone using trained and blinded interviewers after six months and, depending on funding, after 12 and 24 months (see Additional file 1).

### Statistical methods

For the primary outcome measure, the proportion of informed decisions within a treatment group, a generalised linear mixed model, reflecting the hierarchical structure of the data will be used [65]. Due to the relatively small numbers of clusters, imbalances in baseline characteristics on cluster and individual level may occur which are not fully covered by randomisation. Therefore the model will be adjusted for baseline variables. The treatment effect will be analysed at cluster level, whereas covariates will be analysed individually by the model. For the secondary outcome measures linear mixed models or generalised linear mixed methods will be used adjusting for clusters by random effects. These models also allow analyses of subgroups. All analyses will be performed on the intention-to-treat population.

It is planned to perform subgroup analysis of the two groups of patients included in the trial: first, those with a recent diagnosis, facing an initial decision on immunotherapy and second, those considering changing to an oral treatment. Apart from demographic baseline data, all analyses will be cluster-adjusted. We will report causes for study withdrawal for each patient to clarify whether there are any differences between the intervention and control clusters.

In addition, a sensitivity analysis will be performed to evaluate the robustness of study results and to explore different imputation techniques. Altman [66] addressed that there is no ideal method to address missing data. Therefore, different common imputation techniques [67] will be applied and reported with as well as without imputation techniques as suggested by Altman [66]. Last observation carried forward, as well as best and worst case scenario for dichotomous outcomes and multiple imputation techniques, will be conducted in the sensitivity analysis [68].

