**Table 1 Tab1:** **Major endpoints CRCT**

**Instrument**		**Measurement time points**						
		**Enrolment**	**Allocation**	**Post-allocation**				
		**-t** _**1**_	**t** _**0**_	**t** _**1**_	**t** _**2**_	**t** _**3**_	**t** _**4**_	**t** _**5**_
Eligibility screen		X						
Informed consent		X						
Allocation								
Sociodemographic data		X	X					
EDSS			X					
SDMT			X					
MS-related data and resource use			X				X	X
MMIC:								
	Risk knowledge		X			X	X	X
	Attitude			X	X	X		
	Immunotherapy status		X			X	X	X
Dyadic DCS				X (nurse)	X (physician and patient)			
Dyadic MAPPIN’SDM				X (nurse and patient)	X (physician and patient)			
HCR trust scale (Physician/Nurse trust)				X	X			
PBMS			X			X		X
CPS			X			X		X
Decision autonomy						X	X	X
CSES			X			X		X
HAQUAMS			X			X		X
HADS			X			X		X

t_1_ = after last decision coaching; t_2_ = directly after final physician decision encounter; t_3_ = two weeks after final physician encounter; t_4_ = three months after final physician encounter; t_5_ = six months after final physician encounter. CPS: Control Preference Scale; CSES: Coping self-efficacy scale; DCS: Decisional Conflict Scale; EDSS: Expanded Disability Status Scale; HADS: Hospital Anxiety and Depression Scale; HAQUAMS: Hamburg Quality of Life in MS Scale; HCR trust scale: Health care relationship trust scale; MAPPIN’SDM: Multifocal Approach to Sharing in Shared Decision Making; MMIC: Multi-dimensional measure of informed choice; MS: Multiple Sclerosis; PBMS: Planned Behaviour in MS Scale; SDMT: Symbol Digital Modalities Test.

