### Tertiary outcomes (control and safety parameters)

As control parameters we will use measures for anxiety and depression using the Hospital Anxiety and Depression Scale ((HADS) [61]), and disease-specific quality of life using the Hamburg Quality of Life in MS Scale ((HAQUAMS) [62]). Moreover, standard disease-monitoring parameters will be obtained; relapses and disability as measured by Expanded Disability Status Scale ((EDSS) [63]) and the Symbol Digital Modalities Test ((SDMT) [64]) for cognition. Occurrence of relapses will be evaluated at baseline, 14 days, and three and six months after the last physician encounter (for both the IG and CG) using a standardised questionnaire.

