### Harms

As relevant adverse events are unlikely, no interim analyses are planned and no stopping rules will be applied. Nevertheless, safety measures are applied as tertiary endpoints to control for anxiety, depression, and disease-specific quality of life. Furthermore, standard disease monitoring parameters will be collected (such as relapse rate, disability status, and functional status).

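### The secondary-outcome models are described with cluster random effects and no baseline covariate; followed as written, this gives up precision on the secondary scales measured at t0 (CSES, PBMS, CPS)

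*Protocol article*

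**What the plan says.** All of the modelling text is in the Statistical methods section of the protocol article. It first gives the primary outcome a generalised linear mixed model. It then argues that, with so few clusters, chance may leave the two groups unequal at the start, both between clinics and between patients, and draws the consequence: "Therefore the model will be adjusted for baseline variables". Model is in the singular and follows the primary-outcome sentence.

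The secondary outcomes then get their own sentence: "For the secondary outcome measures linear mixed models or generalised linear mixed methods will be used adjusting for clusters by random effects". The only later statement on adjustment is again about clusters: "Apart from demographic baseline data, all analyses will be cluster-adjusted".

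Table 1 ("Major endpoints CRCT") marks PBMS, CPS, CSES, HAQUAMS and HADS at t0, t3 and t5. It shows no t0 measurement for the Decisional Conflict Scale (DCS), MAPPIN'SDM, the trust scale or decision autonomy. HADS and HAQUAMS are not secondary outcomes. The Harms section says "safety measures are applied as tertiary endpoints to control for anxiety, depression, and disease-specific quality of life", and no model is named for the tertiary outcomes.

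**The concern.** The argument used for the primary model, that few clusters leave room for chance imbalance, applies equally to the secondary scales. Yet the article describes their adjustment through clusters alone. A random cluster effect accounts for correlation within clinics. It does not use what a patient's own t0 score says about the later score, and it does not correct for the coached clinics happening to start higher or lower.

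Coping self-efficacy is the subject of the last hypothesis in Aims and objectives, so the precision of that comparison matters to a stated aim. An analysis that took the sentence literally would report wider confidence intervals than the collected data allow.

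**Working it through.** **The plan's own figure.** The Sample size section gives 48% versus 28%, alpha 0.05, 90% power, ICC 0.0045 and 12 clusters of 23.
- Individually randomised, two-sided: 122 per arm.
- Design effect: 1 + (23 − 1) × 0.0045 = 1.099.
- 122 × 1.099 = 134.1 per arm, or 268 in total. 134.1 / 23 = 5.83, rounded up to 6 clusters per arm, which gives 276 evaluable.
- Effective n per arm: 138 / 1.099 = 125.6. Power by the normal approximation is 90.9%.

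The figure reproduces. It concerns the primary outcome and is unaffected by this point. The article states no power for any secondary outcome.

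**Inputs for a secondary scale.**
- 6 clusters of 23 per arm: an assumption from 12 clusters and two groups; the allocation ratio is not stated.
- ICC 0.0045: the plan's value, assumed to hold for the scale.
- Correlation r between t0 and follow-up: not in the document, so 0.3 to 0.7 is assumed, equal at patient and clinic level.

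**Formulas, in SD units.**
- Unadjusted SE of the arm difference: √(2 × 1.099 / 138) = 0.126.
- With the t0 value as covariate, the variance is multiplied by 1 − r². The unadjusted variance is therefore 1 / (1 − r²) times larger than needed: 1 / 0.91 = 1.10, 1 / 0.75 = 1.33, 1 / 0.51 = 1.96. This ratio does not depend on the ICC.
- Difference detectable with 90% power (normal approximation): (1.96 + 1.2816) × SE.

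| Analysis | SE (SD) | Detectable at 90% power (SD) | Power for 0.3 SD |
|---|---|---|---|
| Cluster effect alone | 0.126 | 0.41 | 66% |
| Plus t0, r = 0.3 | 0.120 | 0.39 | 70% |
| Plus t0, r = 0.5 | 0.109 | 0.35 | 78% |
| Plus t0, r = 0.7 | 0.090 | 0.29 | 91% |

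A t reference on 10 degrees of freedom, more cautious with 12 clusters, gives the same ratios. The difference detectable with 80% power is then 0.39 SD unadjusted, and 0.37, 0.34 and 0.28 SD with the t0 value at r = 0.3, 0.5 and 0.7.

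**Carry-over of chance imbalance.** The t0 difference between arms has the same SD, 0.126, so its 95% range is ±1.96 × 0.126 = ±0.25 SD. At assumed ICCs of 0.02 and 0.05 the range is ±0.28 and ±0.34 SD. Without adjustment a share r of the difference passes into the follow-up comparison: a 0.25 SD difference shifts it by about 0.12 SD at r = 0.5 and 0.17 SD at r = 0.7.

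The chance of a t0 difference above 0.2 SD is about 11% at ICC 0.0045 and about 25% at an assumed ICC of 0.05.

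**The case against.** The strongest reply is that the sentence describes how clustering is handled and does not list every covariate. Even for the primary model the article names no baseline variable, and such lists are commonly left to a full protocol or analysis plan that is not shown here. A linear mixed model could also take t0 as a repeated response and recover much of the same precision. This stands in part: a reader might infer that baseline adjustment of secondary outcomes is ruled out, and the text does not say so. What remains is the contrast. The article gives a general reason for baseline adjustment, applies it to the primary model, and then describes adjustment of the secondary models through clusters alone.

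Three further limits stand in full.
- The key secondary endpoint, DCS, has no t0 value, so its own baseline cannot be a covariate.
- At the plan's ICC, clustering adds little to chance imbalance. The SD of the t0 difference is 0.126, against √(2 / 138) = 0.120 with individual randomisation.
- The gain rests on an assumed r and is small at 0.3. If CPS is analysed as a categorical outcome, the 1 − r² figures do not apply to it directly.

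**Conclusion.** The point holds as one of efficiency and conditional imbalance on CSES, PBMS and CPS. At r = 0.5 the unadjusted variance is a third larger than necessary; at r = 0.7 it nearly doubles. These sizes assume a continuous scale, a 6:6 split, 23 analysed per cluster, ICC 0.0045 for the scale and the stated range of r.

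Two stronger readings are not supported.
- A reader might infer that the unadjusted comparisons are biased or have an inflated type I error. Over repeated randomisation they are unbiased, and their standard error already includes chance imbalance. The loss is in precision, and in the estimate conditional on the imbalance that actually occurs.
- A reader might infer that the patient-reported safety comparison is specified without baseline adjustment. HADS and HAQUAMS are tertiary and fall outside the quoted sentence. They would share the weakness only if analysed with the same model.

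**What to change.** In Statistical methods, state that the linear or generalised linear mixed models for secondary outcomes measured at t0 (CSES, PBMS, CPS) include the t0 value of the same outcome as a patient-level covariate in addition to the random cluster effect. Name the same model for HADS and HAQUAMS. Outcomes without a t0 value (DCS, MAPPIN'SDM, trust, decision autonomy) keep the stated model.

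The cost is one sentence, with no new data, visits or patients. The small downside is that missing t0 scores need a simple handling rule, such as baseline imputation, to keep those patients in the model. Few should be missing, because the Screening visit and Baseline data and allocation sections make access to the DECIMS-Wiki follow completion of the baseline questionnaires.

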### Primary outcome

We have previously applied the multi-dimensional measure of informed choice in two controlled trials [52]. Here, informed choice is defined as a compound measure combining three dichotomous measures: risk knowledge, attitude, and therapy uptake. Informed choice encompasses adequate risk knowledge, with either uptake or non-uptake of immunotherapy, and a corresponding (congruent) positive or negative attitude. Attitude will be assessed using a single question directly after the final physician encounter. Uptake will be evaluated from the patient after six months. Risk knowledge will be measured using a previously developed and adapted questionnaire 14 days, and three and six months after the last physician encounter [53]. As applied in a previous trial, the cut off for adequate risk knowledge will be defined *a priori* as the value that 30% of all patients with highest scores reach at baseline. In addition, risk knowledge will be analysed as a continuous variable to enable comparability with other studies. Earlier trials have shown that patients who meet the primary endpoint more often realise their preferences [38,39].

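### Last observation carried forward, planned as a sensitivity analysis, cannot treat the two arms alike for the informed-choice composite, because attitude has an earlier value in the intervention arm only

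*Protocol article*

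**What the plan says.** The section Primary outcome states that "informed choice is defined as a compound measure combining three dichotomous measures: risk knowledge, attitude, and therapy uptake". On timing it adds: "Attitude will be assessed using a single question directly after the final physician encounter". That is t2 in Table 1. Uptake is taken at six months (t5), and knowledge is measured at two weeks, three months and six months after the last physician encounter.

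Table 1 marks attitude at t1, t2 and t3 and leaves baseline (t0) blank. Risk knowledge and immunotherapy status are marked at t0, t3, t4 and t5. The footnote defines t1 as "after last decision coaching".

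The section Control group gives controls the online information tool and usual care, without coaching. For the Decisional Conflict Scale, the section Secondary outcomes labels the assessment after coaching as intervention group and the one after the physician encounter as both groups.

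On missing data, Statistical methods says: "Last observation carried forward, as well as best and worst case scenario for dichotomous outcomes and multiple imputation techniques, will be conducted". The sentence goes on to place all of these in the sensitivity analysis. The purpose given is to examine how robust the results are, and results are to be reported with and without imputation. The same section says: "All analyses will be performed on the intention-to-treat population".

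**The concern.** Carrying an observation forward needs an earlier observation. For the attitude component one exists in the intervention arm and none exists in the control arm. Take two patients who are lost, or skip the question, just before t2. The coached patient has a t1 attitude to carry; the control patient has nothing. The method then handles the arms differently because of the visit schedule, whatever the reason for the missing value.

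The value that would be carried also differs in kind from the one it replaces. It is recorded after coaching but before the physician encounter at which the decision is made. Attitudes from before and after that encounter would be mixed in one arm only.

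What is at stake is the meaning of the robustness check. Agreement or disagreement between this result and the main one would partly reflect the unequal handling, so it could not be read as evidence about missing data.

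**Working it through.** **1. Sources to carry forward, by component and arm** (Table 1, its footnote, and the sections Primary outcome and Control group)

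| Component, time used | Earlier values, intervention | Earlier values, control |
|---|---|---|
| Attitude, t2 | t1 | none |
| Risk knowledge, t5 | t0, t3, t4 | t0, t3, t4 |
| Uptake, t5 | t0, t3, t4 | t0, t3, t4 |

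The t3 attitude exists in both arms but comes after t2, so using it would be filling backwards. Working at the level of the composite does not help: without a baseline attitude, a control patient lost before t2 has no earlier composite to carry.

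**2. The plan's own rates** (Sample size). Informed choice = adequate knowledge × congruence. Intervention: 0.60 × 0.80 = 0.48. Control: 0.40 × 0.70 = 0.28. Difference 20 points. These reproduce.

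**3. Illustration.** The article gives neither a rate of missing t2 attitude nor a rule for cases that cannot be filled. Assumptions:
- m = 10% missing in each arm (borrowed from the overall dropout assumption), with a range of 5 to 15%.
- f = share of the affected intervention patients who have t1, 50 to 100%.
- Filled patients are informed at the same rate as the rest of their arm, which requires their six-month knowledge and uptake to be observed.
- Unfilled patients are scored as not informed.

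Control: 0.28 × (1 − m) = 0.28 × 0.90 = 0.252.

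Intervention: 0.48 × (1 − m + m·f).
- f = 0.5: 0.48 × 0.95 = 0.456; difference 0.456 − 0.252 = 0.204.
- f = 1: 0.48 × 1.00 = 0.480; difference 0.480 − 0.252 = 0.228.

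So 20 points becomes 20.4 to 22.8. For comparison, scoring every missing case in both arms as not informed would give 0.9 × 20 = 18.0 points.

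**4. No true effect, 28% in both arms.** The spurious difference is 0.28 × m × f. At m = 10% it is 0.28 × 0.10 × 0.5 = 1.4 points to 0.28 × 0.10 × 1 = 2.8 points. Over m = 5 to 15% and f = 50 to 100% it runs from 0.7 to 4.2 points.

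**5. Unfilled cases dropped instead.** With 300 patients split equally (150 per arm, an assumption) and m = 10%, evaluable controls number 150 × 0.90 = 135. Evaluable intervention patients number 150 × 0.95 = 142.5 to 150 × 1.00 = 150. If attitude is missing unrelated to outcome, the expected difference stays at 20 points, but the sets compared are selected differently.

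**6. Patients lost altogether before t2.** Here knowledge is carried from baseline too, where about 30% are adequate by the definition of the cut-off. With 80% congruence the filled cases are 0.30 × 0.80 = 24% informed. Even with f = 1, intervention is 0.9 × 48 + 0.1 × 24 = 45.6%, and the difference is 45.6 − 25.2 = 20.4 points.

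**The case against.** The strongest reply is that this is a sensitivity analysis among several. The main result comes from a generalised linear mixed model, and results with and without imputation, including multiple imputation and best/worst case, would stand beside it. That is right, and it limits the weight of the point.

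Second, the affected cases may be few. Attitude is one question asked straight after an encounter, questionnaires can be completed in the clinic, and reminders are sent. Patients lost later in the six months would usually already have t2 attitude. What they lack is later knowledge and uptake, which can be carried in both arms. This stands too; the 10% used above is overall dropout, not a rate for attitude.

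Third, the article lists the method generically and never says that it is meant for attitude, while many other scales have a baseline in both arms. Nor does Table 1 mark the t1 attitude cell as intervention only; that follows from the definition of t1 and from the sections Control group and Secondary outcomes. But the text does not exclude the primary composite either, and on these definitions no t1 assessment can exist for an uncoached patient.

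A reader might infer that the method is bound to favour the intervention, by 2.8 points. The documents do not support that. The figure is an upper end at 10% missing. It rests on a scoring rule that the article does not state and on every affected intervention patient having t1 and six-month data. A t1 attitude may also agree less well with later uptake.

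A reader might also fault the article for not naming one main missing-data method or for not describing imputation by centre. Both are commonly left to an analysis plan, and the article does say that all analyses apart from demographic baseline data are cluster-adjusted.

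**Conclusion.** The point holds in a narrow form. As listed, last observation carried forward cannot be applied evenly to informed choice: a missing t2 attitude has a value to carry in the intervention arm only, and that value predates the decision encounter. A check that handles the arms differently by construction cannot show robustness.

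The primary analysis is not affected, and knowledge and uptake can be carried symmetrically. Under the assumptions stated (10% missing t2 attitude, t1 present for 50 to 100% of those intervention patients, six-month data observed, unfilled cases counted as not informed), the planned 20 points become 20.4 to 22.8. Under another rule the distortion takes another form, and neither its size nor its direction is fixed by the documents. The matter deserves a change of wording; it does not threaten the trial's main conclusion.

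**What to change.** State that last observation carried forward will not be used for the informed-choice composite, or restrict it to outcomes with an earlier measurement in both arms.

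For the composite, rely on the multiple imputation and best/worst case already planned. Impute the three components and score the composite afterwards. Use predictors measured in both arms: knowledge and immunotherapy status at t0, t3 and t4, attitude at t3, arm, and centre. Because each centre belongs to one arm, centre should enter as a random effect, or imputation should be run within arm. Leave the t1 attitude out of the predictors, since it would bring back the same imbalance of information.

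The cost is a little more programming and one fewer sensitivity analysis. No new data are needed.
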